### Safety monitoring

Routine blood test, liver and kidney function test, electrolytes test, and urine test (from baseline to weeks 4) are the basic indicators that reflect the general situation and basic safety evaluation.

### Criteria for discontinuing or modifying allocated interventions

The criteria for discontinuation are as follows: (1) In case of serious adverse events, the clinical experimenter should be stopped according to the doctor’s judgment. (2) If the disease worsens in the course of the disease, or there are other conditions affecting the observation of the study, the clinical experimenter should be stopped and invalid cases should be treated according to the doctor's judgment. (3) Important deviations occurred in the implementation of clinical trial protocols, such as poor compliance, making it difficult to evaluate drug effects. (4) The subject is unwilling to continue the clinical trial during the clinical trial and proposes to the doctor in charge to withdraw from the clinical trial.

For these cases, the reasons for discontinuation shall be recorded in detail. If there is a review, the results of the last major efficacy test shall be taken as the final results for statistical analysis, and the CRF table and REDCap (Research Electronic Data Capture) shall be kept for future reference.

### Strategies to improve adherence to interventions

The drug quantity and date of drug intake by each patient will be recorded. The patients will be required to return any unused drugs during each visit, which will be recorded by the researchers.

### Observation records of adverse events

During the trial period, the adverse event record form should be filled in truthfully. The occurrence, severity, duration, measures taken, and outcome of the adverse event should be recorded. Adverse events should be recorded in the designated clinical case observation form (CRF) adverse event form. The person uses mild, moderate, and severe to describe the intensity of the adverse event and evaluates the possible association between the adverse event and the study drug and combination drug to determine whether it is an adverse reaction. When adverse events are found, the researchers will contact the project leader immediately and start the emergency treatment plan. In case of serious adverse events, the principle of “free treatment first” shall be implemented, and the report shall be reported to the organizer and the ethics committee within 24 h, and the “Serious Adverse Events Report Form” shall be filled out and signed and marked with the date. According to the severity of adverse reactions, the follow-up visit can be in hospital, outpatient, home visit, telephone, communication, and other forms.

### Research process record points

The subject content and data at each time point, according to the patient’s hospitalization period, will be recorded as shown in Table 1. Specifically, the screening period (−3~0 days) will be 0 to 3 days before recruitment. The 4-week treatment period was planned in two cycles of 2 weeks, with a return visit between cycles to check for AEs and monitor compliance. All interventions will be stopped after 4 weeks. Follow-up will be conducted on weeks 4 and 12. The detailed information is shown in Table 3.

**Table 3 Tab3:** Research flowchart

Activity	Phase(time points)	Screening stage	baseline period	intervention	Follow-up	
		−3d~0d	0d	4w	8w	12w
**Enrolment**	Sign informed consent	✔				
	Inclusion and exclusion criteria	✔				
	Demographic data	✔				
	Medical history and treatment history	✔				
	Basic data collection	✔				
**Outcome assessment**	Frequency of atrial fibrillation		✔	✔	✔	✔
	ECG and Holter		✔	✔	✔	✔
	Ultrasonic cardiogram		✔	✔	✔	✔
	TCM clinical syndrome integral		✔	✔	✔	✔
	Rate of increase and decrease of anti-arrhythmia western medicine		✔	✔	✔	✔
	NT-proBNP		✔			✔
	Hamilton Anxiety Scale		✔	✔	✔	✔
	Hamilton Depression Scale		✔	✔	✔	✔
	SF-36		✔	✔	✔	✔
	PVO		✔	✔	✔	✔
	Anaerobic threshold		✔	✔	✔	✔
**Safety assessment**	Physical examination		✔	✔	✔	✔
	Blood routine examination		✔	✔		
	Urine routine and urinary sediment		✔	✔		
	Liver function		✔	✔		
	Renal function		✔	✔		
	Blood lipid		✔	✔		
	GLU		✔	✔		
	INR		✔	✔		
	CHA2DS2-VAS		✔	✔		
	HAS-BCED		✔	✔		
**Other information**	Randomization	✔				
	Hemorrhage		✔	✔	✔	✔
	Readmission		✔	✔	✔	✔

### Sample size

The sample size of this study was calculated based on the analysis of data published in previous articles on the treatment of atrial fibrillation by Chinese medicine and the expected value of efficacy. It was assumed that the total efficacy rates in the study and control groups were 91.1% and 53.3%, respectively [8]. The set *α* = 0.025, *β* = 0.2, superiority limit value*δ*= 10%, and the sample size of each group will be calculated as 30 cases, considering a 20% loss to follow-up, that is, a total of 76 cases.

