### Randomization

This study uses a center-based stratification and block randomization method. The randomization sequence will be generated by study investigators who are statisticians. Patients will be allocated in a 1:1 ratio, aiming to balance baseline characteristics between the groups. Participants will be assigned a PID number, which will be used for subject identification throughout the study. Information regarding the random-number block will be delivered to the participating centers along with the intervention drugs.

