### Statistical analysis

All data are entered using excel worksheets, and SPSS22.0 statistical software is used for statistical analysis. For measurement data, *t* tests are performed for those that conform to the normal distribution, and the data are represented by the mean ± standard deviation; the row-rank conversion that does not conform to the normal distribution For non-parametric test, the data are represented by M (QR). The constituent ratio data uses the *χ*^2^ test. The one-way ordered data uses the rank sum test. *P*>0.05 is not statistically significant, and *P*<0.05 is statistically significant, two-sided test.

To further clarify the research conclusions of this clinical trial, we will perform subgroup analysis by gender or age in the future.

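### The stated inputs do not give 30 per group: the simplest formula needs 34, and 30 evaluable per group has about 75% power, not 80%

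*Protocol article*

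**What the plan says.** All the planning inputs stand in the Sample size section of the protocol article. It assumes that "the total efficacy rates in the study and control groups were 91.1% and 53.3%, respectively". It continues "The set *α* = 0.025, *β* = 0.2" and gives the margin as "superiority limit value*δ*= 10" percent. From these it concludes that "the sample size of each group will be calculated as 30 cases, considering a 20% loss to follow-up", which it takes to 76 patients in all. The Randomization section fixes the ratio: "Patients will be allocated in a 1:1 ratio". The Sample size section neither names a formula nor says whether α = 0.025 is one-sided. The Statistical analysis section sets significance at P < 0.05, which "is statistically significant, two-sided test", and mentions no margin.

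**The concern.** The sample size is presented as the result of a calculation whose inputs are all printed beside it, so it can be checked directly. Showing superiority by more than 10 points when the expected difference is 37.8 points leaves an effective distance of 27.8 points, and 30 per group looked too few for 80% power at one-sided 0.025. If so, the trial claims a power that its design lacks for the hypothesis it was sized on. Readers rely on that figure when they interpret a null or borderline result.

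**Working it through.** **Inputs.** p1 = 0.911, p2 = 0.533, margin δ = 0.10, α = 0.025, β = 0.2, loss 20% (all Sample size section); allocation 1:1 (Randomization section). α is read as one-sided, which matches the two-sided 0.05 of the Statistical analysis section and favours the plan.

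**The plan's own total.** 30/(1 − 0.20) = 37.5, rounded up to 38; 38 × 2 = 76. This reproduces, and it shows that 30 is the evaluable number per group after losses. The question is where 30 comes from.

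**Sample size, unpooled variance.**

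n = (z₁₋α + z₁₋β)² × [p1(1 − p1) + p2(1 − p2)] / (p1 − p2 − δ)²

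- (1.960 + 0.842)² = 7.849
- 0.911 × 0.089 + 0.533 × 0.467 = 0.0811 + 0.2489 = 0.3300
- (0.378 − 0.10)² = 0.278² = 0.0773
- n = 7.849 × 0.3300 / 0.0773 = 33.5, so **34 per group**

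**Other formulas with every stated input (one-sided 0.025 unless noted).**

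| Method | n per group | Rounded up |
|---|---|---|
| Arcsine, control rate shifted by the margin | 32.4 | 33 |
| Unpooled | 33.5 | 34 |
| Farrington-Manning | 37.05 | 38 |
| Mixed variance (pooled under the null, unpooled under the alternative) | 38.5 | 39 |
| Unpooled with continuity correction | 40.4 | 41 |
| Unpooled, α = 0.025 read as two-sided | 40.6 | 41 |
| Pooled | 40.8 | 41 |

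The pooled line uses a mean rate of 0.722 and variance 2 × 0.722 × 0.278 = 0.4014. None of these gives 30.

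**Power at 30 evaluable per group.**

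- Standard error = √(0.3300/30) = 0.1049
- 0.278/0.1049 − 1.960 = 2.651 − 1.960 = 0.691, so power = **75.5%**

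Power against the margin, by the same formula and by exact binomial enumeration of three tests:

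| Evaluable per group | Formula | Exact Wald | Exact Farrington-Manning score | Exact Newcombe |
|---|---|---|---|---|
| 30 | 75.5% | 75.5% | 74.0% | 71.8% |
| 34 | 80.6% | 80.1% | 77.9% | 77.0% |
| 38 | 84.7% | 83.5% | 81.8% | 81.6% |

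The more conservative approximations are lower at 30: 70.8% (Farrington-Manning) and 68.8% (mixed variance).

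**Randomised numbers for 80% power with 20% loss.** 34/0.8 = 42.5, so 43 per group and 86 in total. If 38 evaluable are needed, 38/0.8 = 47.5, so 48 per group and 96 in total.

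**What it takes to reach about 30.** A stated input has to change: power 75% (29.6, unpooled), a margin of 8 points (30, unpooled), or one-sided α = 0.05 (29.03 by Farrington-Manning, 30.1 by mixed variance). Dropping the margin does not lead there by the uncorrected formulas: unpooled variance gives 18.1 at one-sided 0.025 and 22.0 at two-sided 0.025, and mixed variance gives 20.8 and 25.4. A continuity correction brings the two-sided 0.025 case to 31. The document does not show which route, if any, was taken.

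**The case against.** The strongest reply is that the shortfall concerns only superiority by more than 10 points, whereas the Statistical analysis section describes ordinary two-sided tests at 0.05 without a margin. For a plain comparison of the two rates, 30 per group has about 92.5% power by the normal approximation and about 94% by exact enumeration of the χ² test. That is true: the trial is not short of patients for that simpler question. It does not rescue the paragraph, which sizes the trial on a 10-point margin and states β = 0.2 for it. It shows instead that the margin in one section and the tests in the other have to be reconciled.

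A second reply is that the article names no formula and may leave it to the full protocol, so 34 is too definite. This stands in part. The figure depends on the formula, and 33 to 41 is the honest range; 34 belongs to the unpooled version. But no formula tried returns 30 from the printed inputs, and condensing a protocol does not explain a result that disagrees with the inputs beside it.

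A third reply is that 38 per group gives 82% to 85%. That holds for the unpooled formula and the exact tests (the mixed-variance formula gives 79.4%), but only if nobody is lost, while the plan assumes 20% loss.

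**Conclusion.** The point holds. With its own rates, margin, α and β, the plan needs 34 evaluable patients per group by the unpooled formula, and 33 to 41 across the methods tried; it states 30. At 30, power against the 10-point margin is about 75% (72% to 75.5% by exact enumeration, as low as 69% by the mixed-variance approximation) instead of 80%. The gap is moderate: 4 evaluable patients per group, or 10 randomised in total (86 against 76), on a lenient reading. This rests on α = 0.025 being one-sided, on the printed rates being true, and on the full 20% loss. It makes no allowance for the interim analysis at 44 patients; any adjustment of α for that look would lower power further.

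**What to change.** Rewrite the Sample size paragraph so that its figures agree. Suggested content: 76 patients randomised, leaving about 30 evaluable per group after 20% loss, give about 75% power to show superiority by more than 10 percentage points at one-sided α = 0.025 if the rates are 91.1% and 53.3% (unpooled normal formula); with no loss, power is about 85% by the same formula. Name the formula and state the sidedness of α.

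If 30 came from other inputs, give those inputs instead. In either case, say in the Statistical analysis section whether the primary comparison is tested against the 10-point margin or against zero, so that the quoted power belongs to the planned test.

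The cost is wording only. The stated power becomes less favourable, and no additional patients are needed. Only if the sponsor wants to keep the 80% claim for the margin hypothesis would the target have to rise, to at least 86 randomised by the unpooled formula.

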### Recruitment

Participants will be recruited from the Longhua Hospital affiliated to Shanghai University of Traditional Chinese Medicine by the researchers who have a Good Clinical Practice certificate. The patients will be informed about the objectives, approaches, potential adverse effects, and advantages of this trial. The planned enrollment period is 21 weeks.

We will use three main ways to ensure enough participants in our project:
Posting recruitment information in the hospital area (such as outpatient lobby and ward door);Posting recruitment information on popular communication platforms such as WeChat public account and hospital service account;If potential participants are found in the outpatient and inpatient staff of the Longhua Hospital, the researchers will ask the patients if they are willing to participate

### Confidentiality

Only the investigator participating in the research clinical trial will have access to the subject’s personal medical records, and they will sign an “Investigator statement” or “Confidentiality Commitment” that includes confidentiality. Data will be processed in a “data anonymity” manner, and the information that can identify the individual identity of the subject will be omitted.

### Statistical analysis

All data are entered using excel worksheets, and SPSS22.0 statistical software is used for statistical analysis. For measurement data, *t* tests are performed for those that conform to the normal distribution, and the data are represented by the mean ± standard deviation; the row-rank conversion that does not conform to the normal distribution For non-parametric test, the data are represented by M (QR). The constituent ratio data uses the *χ*^2^ test. The one-way ordered data uses the rank sum test. *P*>0.05 is not statistically significant, and *P*<0.05 is statistically significant, two-sided test.

To further clarify the research conclusions of this clinical trial, we will perform subgroup analysis by gender or age in the future.

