### Inclusion criteria

The inclusion criteria are as follows: (1) The patient’s age is 18–85 years; (2) atrial fibrillation, seizure frequency ≥2 times a month (at least one ECG diagnosis); (3) the main syndrome of TCM syndrome differentiation was Qi deficiency-caused phlegm stagnation; and (4) have a correct understanding of the significance of the study, have good compliance with the observation and evaluation of the researcher, and voluntarily accept the clinical trial and fill in the clinical consent form.

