### Outcomes

#### Primary outcome

Frequency of atrial fibrillation attacks (from baseline to weeks 4, 8, and 12)
° Significant effects: The frequency of attacks decreased by more than 70%.° Effective: The frequency of attacks decreased between 30% and 70%.° Invalid: The frequency of attacks decreased by less than 30%.° Deterioration: Increased attack frequency.

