#### Secondary outcomes

Echocardiography (from baseline to weeks 4 and 12): Echocardiographic measurement of LVEF, SV, left ventricular end-diastolic diameter (LVEDD), left ventricular end-systolic diameter (LVESD), ratio of left ventricular early diastolic fast filling peak to late diastolic filling peak (E/a), and ratio of early diastolic velocity of mitral valve to early diastolic annular velocity (E/e).Hamilton Anxiety Scale, Hamilton Depression Scale (from baseline to weeks 4, 8, and 12). HAMA is mainly used to assess the severity of patients’ anxiety symptoms, generally more than 14 points considered meaningful. HAMD is one of the most commonly used scales to assess depression in clinical practice, and more than 20 points are considered meaningful.Rate of increase and decrease of anti-arrhythmia western medicine (from baseline to weeks 4, 8, and 12).SF-36 (from baseline to weeks 4, 8, and 12). The MOS Item Short from Health Survey (SF-36) was used to evaluate the quality of life of patients.NT-proBNP (from baseline to weeks 4 and12): NT-proBNP is a reliable and sensitive indicator of heart failure. One of the causes of heart failure is atrial fibrillation. Its elevation is positively correlated with the severity of heart failure. Changes in the levels of NT-proBNP in each group will be measured before and after treatment.Integral TCM syndrome score (from baseline to weeks 4 and 12; the scores and details are presented in Tables 1 and 2): A scale of 0–6 points and half quantitative points will be used to score the patients according to the severity of clinical symptoms [7].
° Significant effect: inhibition or complete suppression of primary and secondary clinical symptoms and reduction of syndrome score by ≥ 70%° Effective: significant improvement in clinical symptoms, and reduction of syndrome score by 30–70%° Ineffective: reduction of treatment syndrome score by < 30%° Aggravation: the score after treatment exceeds the score before treatment

**Table 1 Tab1:** Traditional Chinese Medicine symptom score

	None	Mild	Moderate	Severe
Palpitation	0	2	4	6
Panting	0	2	4	6
Lassitude	0	2	4	6
Expectoration	0	2	4	6
Weight	0	2	4	6
Tongue fur and type of pulse	0	2	4	6

**Table 2 Tab2:** Detailed description of symptoms according to Traditional Chinese Medicine

	None	Mild	Moderate	Severe

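### No planned test adjusts for the baseline value, and the primary's percent-change classes are coarse at low attack counts; both cost precision, not validity

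*Protocol article*

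**What the plan says.** The protocol article's Statistical analysis section gives one set of tests for all outcomes. For normally distributed measurements, t "tests are performed for those that conform to the normal distribution, and the data are represented by the mean ± standard deviation". Non-normal measurements get an unnamed non-parametric test, proportions a chi-square test, and for ordered categories: "The one-way ordered data uses the rank sum test". Significance is at 0.05, two-sided. No regression or covariance model is named. The section does not say whether a measurement is compared as a follow-up value or as a change.

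The primary outcome is "Frequency of atrial fibrillation attacks (from baseline to weeks 4, 8, and 12"), sorted into four ordered classes by percent change: a fall of more than 70%, a fall of 30-70%, a fall of less than 30%, and an increase. Entry requires "seizure frequency ≥2 times a month".

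Among the secondary outcomes, change is explicit for NT-proBNP ("Changes in the levels of NT-proBNP in each group will be measured before and after treatment"), for the TCM syndrome score (percent-reduction classes) and for the increase or decrease of anti-arrhythmic medication. Echocardiography, the two Hamilton scales and SF-36 carry only a baseline-to-week label. Table 3 schedules a baseline measurement for every efficacy outcome.

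**The concern.** The baseline value of a continuous outcome usually predicts its follow-up value. A two-sample test on follow-up values leaves that information unused. A test on change uses it with a fixed weight of one, which is rarely the best weight. ANCOVA estimates the weight and, in large samples, is never less precise than either. The Sample size section plans for 30 evaluable patients per arm, so precision is scarce.

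The primary has a related weakness. A percent change computed from a small integer takes few values. What one attack fewer means therefore depends on where the patient started, and the classes discard much of what the counts contain. What is at stake is the chance of detecting a real effect and the width of the intervals, at a point where the data needed to do better are already being collected.

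**Working it through.** **The plan's own size.** 30 / 0.8 = 37.5, so 38 per arm and 76 in total, as stated. The 30 itself does not follow from the stated inputs by the usual unpooled formula: 7.849 × (0.911 × 0.089 + 0.533 × 0.467) / (0.911 − 0.533 − 0.10)² = 7.849 × 0.330 / 0.0773 = 33.5. That is a separate matter. Here 30 evaluable per arm is taken as planned.

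**Continuous outcomes.** Let r be the baseline-to-follow-up correlation, with equal variances. The protocol gives no value, so r is assumed. The variance of the treatment difference is proportional to:
- follow-up value only: 1
- change: 2(1 − r)
- ANCOVA: 1 − r²

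ANCOVA against follow-up is therefore 1 − r². Against change it is (1 − r²) / (2(1 − r)) = (1 + r)/2.

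| r | ANCOVA / follow-up | ANCOVA / change |
|---|---|---|
| 0.3 | 0.91 | 0.65 |
| 0.5 | 0.75 | 0.75 |
| 0.7 | 0.51 | 0.85 |

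At r = 0.5, 60 patients analysed by ANCOVA carry the information of 60 / 0.75 = 80 analysed by either t test.

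In terms of power, take the difference that gives a follow-up-only test 80% power at 30 per arm: (1.960 + 0.842) × √(2/30) = 0.723 SD (normal approximation). At r = 0.3, 0.5 and 0.7, ANCOVA has 84%, 90% and 97.5% power. A test on change has 66%, 80% and 95%.

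**Primary classes at low counts.** This part needs no assumption.

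| Baseline | 1 fewer | 2 fewer | 3 fewer |
|---|---|---|---|
| 2 | 50% (effective) | 100% (significant) | – |
| 3 | 33% (effective) | 67% (effective) | 100% (significant) |
| 4 | 25% (invalid) | 50% (effective) | 75% (significant) |

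If a patient's true monthly rate stays equal to the baseline count and counts are Poisson (assumed), chance alone gives effective or better in 0.135 + 0.271 = 41% at a baseline of 2, 0.050 + 0.373 = 42% at 3, and 0.092 + 0.147 = 24% at 4.

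**Power for the primary.** The attack-rate distribution and rate ratios are not in the protocol, so two sets of simulations with assumed values were used. All have 30 per arm, entry at 2 or more attacks, and two-sided 0.05. The comparator is a quasi-Poisson model of the count with log baseline count.

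Set A: gamma-Poisson counts, shape 2, rate ratio 0.6, 3,000 trials per setting.

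| Mean attacks per 4 weeks | Chi-square, fall ≥30% | Rank sum, 4 classes | Count model |
|---|---|---|---|
| 3 | 56% | 65% | 77% |
| 5 | 71% | 80% | 91% |
| 8 | 85% | 91% | 97% |

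Loss against the count model: rank sum 12, 11 and 6 points; chi-square 21, 20 and 12 points.

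Set B: seven scenarios, overdispersed counts, mean 3-10 a month, rate ratios 0.3-0.5 on HTDJ and 0.7-0.8 on control, 1,000 trials each (Monte Carlo error about 1.5 points). Power ranges are chi-square 30-82%, rank sum 37-92% and count model 48-98%. The loss is 6-14 points for rank sum and 16-24 for chi-square.

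Taken together: about 6-14 points for rank sum and 12-24 for a responder chi-square. With no treatment effect, every test rejected in roughly 4-5% of trials in both sets.

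**The case against.** The case against has several parts, and much of it stands.

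- A reader might infer that the tests ignore baseline altogether. The text does not support that. Percent-change classes use baseline as the denominator, and a t test on change subtracts it. Only a test on follow-up values would ignore it, and the section does not say which is meant. What is absent is baseline as a covariate.
- A reader might infer that every outcome is defined as a change. For echocardiography, the Hamilton scales and SF-36, the baseline-to-week label may simply be a visit schedule.
- A reader might infer false positives from chance responders (28-44% of patients under set A with no effect) or from regression to the mean after selection on at least 2 attacks. Both act alike in the two randomised arms. They dilute the contrast without biasing it, and type I error is kept.
- The Statistical analysis section assigns ordered data to the rank sum test, so the smaller loss is the direct reading for a four-class primary. The larger loss arises only if the classes are collapsed. The Sample size section, which works with a total efficacy rate, makes that possible but does not fix it.
- The power figures are not this trial's. At the planned 91.1% v 53.3%, a plain two-sided chi-square with 30 per arm and no margin has about 93% power.
- Adjusting a logistic primary would be fragile. At 91.1% response only 30 × 0.089 = 2.7 non-responders are expected on HTDJ, with a 0.911³⁰ = 6% chance of none.
- Model form is often left to an analysis plan, and none is shown. This stands in part. The article is not silent, however: it names a specific set of unadjusted tests. If a fuller plan already adjusts for baseline, the article's text should be brought into line with it.

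**Conclusion.** The point holds as a matter of efficiency. The article commits to unadjusted two-sample tests, leaves open whether they use change or follow-up values, and makes no covariate use of baselines that it collects. For the continuous outcomes the variance formulae are exact given r; only r is assumed. The saving from ANCOVA is 25% against either t test at r = 0.5, and 49% (follow-up) or 15% (change) at r = 0.7.

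For the primary, the coarseness at 2-4 attacks is plain arithmetic. Its cost in power is moderate with the rank sum test and larger only if the classes are collapsed. Both ranges depend on assumed attack rates and effect sizes and should be labelled so. The higher power belongs to the count model, which is proposed below only as supportive, so the fix does not raise the power of the primary test itself. Nothing here shows bias or an inflated error rate.

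**What to change.** In the Statistical analysis section:

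1. State that the continuous outcomes (echocardiographic measures, HAMA, HAMD, SF-36, total TCM score, and NT-proBNP on the log scale) are compared at each scheduled follow-up visit by ANCOVA of the follow-up value, with treatment group and that outcome's baseline value as terms, reporting the adjusted difference with its 95% confidence interval. This also settles the question of change versus follow-up value.
2. Keep the primary as the four-class or responder comparison, and say which of the two is tested.
3. Pre-specify one supportive analysis of the primary data: a negative binomial or quasi-Poisson model of the attack count, with treatment, log baseline count and an offset for log observation time, reporting the rate ratio with its 95% confidence interval.
4. If power is quoted for the supportive model, give the assumed attack rates and effect sizes beside it.

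The cost is a few lines of text, slightly more modelling than two-sample tests, and one extra supportive result that may differ from the primary. No new measurements are needed beyond recording the days over which attacks were counted.

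### The trial is sized for a difference above 10 points in a binary efficacy rate, but every listed test is a no-margin test, none is tied to the primary outcome, and the stated 80% power fits none of the candidate binary analyses

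*Protocol article*

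**What the plan says.** Three sections of the protocol article bear on the primary comparison.

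- **Sample size.** The planning assumption is that "total efficacy rates in the study and control groups were 91.1% and 53.3%, respectively". With alpha 0.025, beta 0.2 and a superiority limit, the text continues "10%, and the sample size of each group will be calculated as 30 cases", and then "considering a 20% loss to follow-up, that is, a total of 76 cases". This is a binary endpoint with a margin: the hypothesis being sized is that the difference exceeds 10 points.
- **Primary outcome.** Attack frequency is followed from baseline to weeks 4, 8 and 12 and graded in four ordered classes. One of them reads "Effective: The frequency of attacks decreased between 30% and 70"%; the others are a larger decrease, a smaller decrease, and an increase. No total efficacy rate is defined.
- **Statistical analysis.** Tests are listed by type of data: t test or a non-parametric test for measurements, chi-square for proportions, and for ordered grades "The one-way ordered data uses the rank sum test". The decision rule is two-sided P<0.05. There is no margin, shifted null or confidence limit, and no test is assigned to the primary outcome.

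**The concern.** A sample size is a statement about one hypothesis, one endpoint and one test. Here the endpoint used for sizing (a binary rate) is not the endpoint defined (four grades), and the hypothesis used for sizing (a difference above 10 points) is not one that any listed test addresses. The conflict does not depend on which test is used. If the grades are compared as ordered data, the endpoint form differs and there is no margin. If they are collapsed and compared by chi-square, the null is still a zero difference.

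Two things are at stake. A reader of the Sample size section could take a significant result as showing superiority by more than 10 points when it does not. And the stated 80% power describes none of the binary analyses that could be meant.

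**Working it through.** **Inputs.** Sample size section: p1 = 0.911, p2 = 0.533, margin 0.10, alpha 0.025 (sidedness not stated; read as one-sided), power 0.80, 30 evaluable per arm, 20% loss, 76 in total. Randomization section: "Patients will be allocated in a 1:1 ratio". Statistical analysis section: two-sided 0.05, no margin.

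**1. The plan's own figure.** The dropout step reproduces: 30/(1 − 0.2) = 37.5, so 38 per arm and 76 in total. The 30 does not follow from the stated inputs by the usual unpooled formula for superiority by a margin:

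n = (z₀.₉₇₅ + z₀.₈₀)² × [p1(1−p1) + p2(1−p2)] / (p1 − p2 − 0.10)²
= 7.849 × (0.0811 + 0.2489) / 0.278²
= 7.849 × 0.3300 / 0.0773 = 33.5, so 34 per arm.

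Without the margin, the standard two-proportion formula at two-sided 0.05 gives 21 per arm. The stated 30 lies between the two.

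**2. Power at 30 per arm under each hypothesis.**

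- Against the 10-point margin (Wald): 0.278 / √(0.3300/30) = 2.651, and Φ(2.651 − 1.960) = 75.5%. Exact binomial enumeration also gives about 75.5%. With the Miettinen-Nurminen statistic, exact power is 72.0%.
- Against zero (chi-square): pooled rate 0.722, √(2 × 0.722 × 0.278) = 0.6336, √0.3300 = 0.5744. Φ[(0.378 × √30 − 1.960 × 0.6336) / 0.5744] = 92.5%. Exact enumeration gives 93.6%.

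Neither is 80%.

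**3. Results that meet one rule and not the other** (30 per arm, control 16/30):

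| HTDJ | Difference (points) | z against zero | P | 95% lower limit, Wald | 95% lower limit, Miettinen-Nurminen |
|---|---|---|---|---|---|
| 24/30 | 26.7 | 2.19 | 0.028 | 3.8 | 2.7 |
| 25/30 | 30.0 | 2.50 | 0.012 | 7.7 | 6.5 |
| 26/30 | 33.3 | 2.82 | 0.005 | 11.7 | 10.4 |

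So 24 and 25 responders satisfy the P<0.05 rule without showing a difference above 10 points; 26 is the first count that clears the margin.

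**4. Whether the choice between rank sum and chi-square matters.** Two made-up tables with 30 per arm, grades ordered best to worst:

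- HTDJ 16/6/6/2 against control 6/12/8/4: rank sum P = 0.028; chi-square on the top two grades (22 against 18) P = 0.27.
- HTDJ 4/20/5/1 against control 10/6/10/4: rank sum P = 0.56; chi-square (24 against 16) P = 0.028.

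The two candidate tests can give opposite answers in either direction.

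**The case against.** **The full protocol or a SAP may settle the primary test.** This is an article, and naming the test, collapsing the grades and fixing a success rule are commonly left to those documents. That stands as far as it goes: the absence of such detail is not the point here. What remains is that one section states a margin and another states a decision rule without one. No further document can satisfy both as written.

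**A reader might infer that the plan sends the primary outcome to the rank sum test.** The article does not say so. The list is by data type, and the rank sum sentence could equally serve the four-class TCM syndrome grading. Attack frequency as a count could fall under measurements, and a total efficacy rate would go to chi-square. Rank sum is the natural reading for the grades, but it is an inference. The conflict survives because no listed test carries a margin.

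**A reader might infer that the trial risks a false claim of efficacy.** With a true difference of exactly 10 points, the no-margin test favours HTDJ about 12% of the time at 63.3% against 53.3%, and about 19% at 90% against 80%. Those are errors only against the margin null, so they matter only if the report claims that the margin was exceeded. The Study objectives section promises an evaluation of efficacy and safety and sets no such claim. A test against zero keeps its own error rate and has more power than planned. This limits the harm.

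**One-sided 0.025 and two-sided 0.05 agree in the favourable direction.** Correct, and the point does not rest on alpha.

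**That 30 per arm is not reproduced is a separate sample-size matter.** Agreed. It adds no weight to this point, although it affects the cost of keeping the margin.

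**Conclusion.** The conflict is real and lies within the article: the trial is sized for a difference above 10 points in a binary rate, while the outcome is defined as four grades and every listed test is a no-margin test at two-sided P<0.05. At 30 per arm and the planning rates, power is about 94% (exact) against zero and about 72–75% against the margin, so 80% belongs to neither. A result of 24/30 against 16/30 would count as significant with a lower limit of about 3 to 4 points.

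This rests on reading alpha 0.025 as one-sided, on the planning rates being true, and on 30 evaluable patients per arm. It should be fixed, because the meaning of a positive result depends on it. It does not invalidate the trial: a plain test of any difference remains a legitimate test of efficacy. That the sized hypothesis will never be tested at all cannot be concluded from this article alone.

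**What to change.** Name one primary analysis at one stated time point among weeks 4, 8 and 12. Define the total efficacy rate, for example as the two best grades combined, which the sponsor must confirm because the article does not define it. Make the rank sum test on the four grades supportive. Then choose one of two routes.

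- **(a) Drop the margin.** Delete the 10% limit from the Sample size section and restate power for the zero-difference test: about 93% at 30 per arm. Cost: wording only, but the trial gives up any claim of a difference above 10 points.
- **(b) Keep the margin.** Claim superiority only if the lower limit of the two-sided 95% confidence interval for the difference exceeds 10 points, name the interval method, and restate power at 30 per arm as about 72–75%. Cost: success is harder to claim and the stated power falls below 80%. Restoring 80% would need about 34 evaluable per arm by the unpooled formula: 34/0.8 = 42.5, so 43 per arm and 86 in total instead of 76. The Farrington-Manning variance would need 38 evaluable per arm.

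Whichever route is taken, the choice should be recorded before any unblinded comparison is seen.
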